### Proposed sample size/power calculations

In a previous group-based MoVo-LISA trial with orthopedic patients, exercise duration was 156 min/week immediately after the intervention, which decreased to 92 min/week at 6 months after discharge [16]. If the MoVo-App is able to stabilize the post-treatment effect, a medium effect size of (standardized mean difference) *d* = 0.62 for the main effect and a small to medium effect size for the interaction effect group (MoVo-LISA + MoVo-App) × time of *d* = 0.35 at the 6-month follow-up (T4) can be expected. However, the effect size estimate for the interaction effect could only be extrapolated from interaction effects observed for group trials comparing MoVo-LISA with a wait-list control group [19]. We assume a baseline measure of the outcome to be used as a covariate and a correlation between pre- and postmeasures of 0.33 based on prior data. With a power of 80%, a significance level of 5%, and small to moderate effect sizes, and considering an estimated dropout rate of 15%, a total sample size of 224 is required.

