### Inclusion criteria

Patients are included if they fulfill the following inclusion criteria: (1) age 18 years or older; (2) musculoskeletal diagnosis classified in chapter M of the International Statistical Classification of Diseases and Related Health Problems, 10th Revision (ICD-10) [42], diagnosed by a physician; (3) sufficient knowledge of the German language; (4) ownership of a smartphone and internet access for online assessments; and (5) being physically inactive (sport activity < 30 min/week) in the last 3 months. Exclusion criteria are (1) rehabilitation following inpatient clinic treatment (e.g., due to surgery) and (2) not able to exercise for medical reasons. Eligible patients receive an invitation to participate in the study, an information letter/leaflet, and the informed consent form and complete the baseline online questionnaire (T0) during a study information meeting with a study assistant.

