To assess the mediating and moderating effects of psychosocial factors, the linear mixed-effects model of repeated measures will be extended by including psychosocial factors as random effect covariates. Their added effect as covariates, their interaction with IG, and a three-way interaction with IG and time will be estimated. It will be considered whether and how psychosocial intermediary effects depend on the intervention. Effects will be considered significant if *p* < 0.05.

The analysis does not consider a cluster effect of using two sites for the intervention. This decision is based on the high standardization in the delivery of the intervention and all study procedures in both sites. Differences in patient population between clinics will be accounted for by including demographic and clinical variables as covariates in the analysis. Furthermore, clinic was also used as a stratification factor in the randomization scheme (as detailed above).

Standardized mean differences and 95% confidence intervals will be calculated to measure the between-group effect size at post-treatment (T3) and follow-up (T4, T5). All analyses will be performed on an intention-to-treat basis. Completer (per-protocol) analyses will be conducted to investigate the influence of study attrition on study results. In addition, we will analyze the extent to which participants adhere to physical activity in accordance with the National Recommendations for Physical Activity and Physical Activity Promotion [77].

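### The stated inputs do not give N = 224: for a two-sided, baseline-adjusted comparison at 6 months with d = 0.35, 224 randomised gives about 72% power, not 80%

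*Protocol article*

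**What the plan says.** The section on proposed sample size and power calculations names two effects: a main effect of d = 0.62, and a group × time interaction at the primary time point, "time of *d* = 0.35 at the 6-month follow-up (T4) can be expected". It assumes that baseline enters as a covariate, with "a correlation between pre- and postmeasures of 0.33 based on prior data". The calculation is then given in one sentence, which opens "With a power of 80%, a significance level of 5%, and small to moderate effect sizes" and ends "considering an estimated dropout rate of 15%, a total sample size of 224 is required".

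The section names no formula and no sidedness, and does not say which of the two effects fixed the total. Elsewhere the article gives 1:1 allocation (Study design) and plans to analyse the 6-month outcome with its baseline value as covariate, within a linear mixed model over T1 to T5 (Statistical analyses). Significance is p < 0.05, and the effect estimates come with 95% intervals: "Standardized mean differences and 95% confidence intervals will be calculated to measure the between-group effect size".

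**The concern.** The article gives almost everything needed to check its own total, and the obvious check fails. The smaller effect should drive the sample size, and with d = 0.35 and a covariate correlation of 0.33 the requirement before any dropout is already slightly above 224. A total that is said to include 15% dropout should be well above that.

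The stated power matters because enrolment ended in December 2019 and the number cannot be raised. The trial compares an add-on app with an active programme, and the section itself says that the interaction effect was extrapolated from comparisons with a wait-list control. A null result is therefore realistic, and readers would weigh it against a claimed type II error of 20%. On the reading closest to the text, that error is about 28%.

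**Working it through.** **Inputs**, all from the sample size section except allocation (Study design): d = 0.35 at 6 months; r = 0.33; 5% level; 80% power; 15% dropout; 1:1. Two-sided testing is my assumption, based on the plain 5% level and the 95% intervals.

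**Attempt to reproduce 224.** For a baseline-adjusted comparison the variance factor is 1 − r² = 1 − 0.33² = 0.8911.

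n per arm = 2 × (1.96 + 0.8416)² × 0.8911 / 0.35² = 114.2, so 115 per arm and 230 in total. With the noncentral t distribution it is 116 per arm and 232 in total.

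With 15% dropout: 230 / 0.85 = 270.6, so 271; 232 / 0.85 = 272.9, so 273. Multiplying by 1.15 instead gives 265. None of these is 224.

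**Power at the stated total.** 224 × 0.85 = 190.4, so about 190 analysed, 95 per arm.

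- Normal approximation: 0.35 × √(95 / (2 × 0.8911)) − 1.96 = 0.595, power 72.4%. Noncentral t: 72.0%.
- Effect detectable with 80% power: 2.8016 × √(2/95 × 0.8911) = 0.384.
- If all 224 were analysed: 78.9% (noncentral t).

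**Other readings**, with 5% level, 80% power and N/(1 − 0.15) for dropout (normal approximation unless noted):

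| Reading | Analysable | Randomised |
|---|---|---|
| Two-sided, baseline covariate, d = 0.35 | 230 | 271 |
| Two-sided, no covariate, d = 0.35 | 258 | 304 |
| Two-sided, change score, variance factor 2(1 − r), d = 0.35 | 344 | 405 |
| Two-sided, baseline covariate, d = 0.62 | 74 | 88 |
| One-sided, baseline covariate, d = 0.35 | 180 (182 with t) | 212 (about 215 with t) |
| One-sided, no covariate, d = 0.35 | 202 | 238 |
| Repeated-measures F test, interaction, two measures, f = 0.175 | 88 | 104 |
| Repeated-measures F test, between groups, two measures, f = 0.175 | 173 | 204 |

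Repeated-measures forms with three to six measures give smaller totals still. The nearest miss is a one-sided test with √(1 − r²) wrongly used as the variance factor: 192 analysable, then 226 (or 221 with × 1.15). No reading tried returns 224.

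**What would make 224 fit.** With 190 analysed and a two-sided test, 80% power needs d of about 0.38 with r = 0.33, or r of about 0.51 with d = 0.35. The section states neither.

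**Optional sensitivity figures (assumptions).** Entry is limited to patients "being physically inactive (sport activity < 30 min/week) in the last 3 months", which may weaken the baseline correlation. At the extreme of r = 0, power with 190 analysed is 67%. The Background cites 23% average attrition in the intervention groups of internet-delivered programmes. If that applied to both arms (about 86 per arm), power would be 68% with r = 0.33.

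**The case against.** The strongest objection is that 72% belongs to one contrast. The section attaches d = 0.35 to a group × time interaction, and the planned analysis is a mixed model over several time points. Under the two-measure repeated-measures formulas above, 104 or 204 randomised would do, so 224 would give more than 80% power. A one-sided 5% test would also be covered, with about 82% power at 190 analysed. For d = 0.62, power at 190 is about 99%. A mixed model also keeps partial data from patients who drop out, and further covariates could reduce residual variance.

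This stands to the extent that 72% must be given with its conditions. It does not rescue the stated figure. The section ties d = 0.35 to 6 months, names a baseline covariate with one pre-post correlation, and mentions neither a one-sided test nor a repeated-measures formula. None of these alternatives returns 224 either. Nor do all readings of the interaction favour the plan: a change from baseline, with d in raw outcome SD units, would need 405.

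A reader might also infer that the 15% was never added, since 224 is near the pre-dropout requirement of 230. That is possible but not shown. The text says that dropout was considered, 224 analysed would still fall just short of 80%, and 190 / 0.85 = 223.5 also rounds up to 224.

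**Conclusion.** The stated total does not follow from the stated inputs. Read as a two-sided, baseline-adjusted difference at 6 months with d = 0.35 and r = 0.33, the design needs 271 to 273 randomised, about 47 to 49 more than 224. At 224 it has about 72% power for d = 0.35, or 80% for d of about 0.38. This rests on a two-sided 5% test, a single follow-up measure, and 15% loss giving about 190 analysed.

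A reader might go further and call the trial underpowered outright, or say that only a one-sided test could justify 224. The documents support neither claim, because the power depends on a test and contrast that the section does not name, and a repeated-measures formula would also make 224 sufficient. The r = 0 and 23% attrition figures are bounds under added assumptions. The prior data behind r = 0.33 are not shown, and the Background argues that blended programmes may lose fewer patients. The conclusion needs neither figure.

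**What to change.** Keep N = 224. In the sample size section, state the test, its sidedness and the contrast that was powered, and replace the 80% claim with wording such as: 224 randomised, about 190 analysed after 15% dropout, gives about 72% power for d = 0.35 in a two-sided 5% comparison at 6 months adjusted for baseline (r = 0.33), or 80% power for d of about 0.38. If a different calculation was used, show it with its formula and inputs; if it reproduces 224, the 80% can stay. The r = 0 and 23% attrition cases may be added as sensitivity figures but are not required.

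The cost is wording only: recruitment, design and analysis do not change. Unless the calculation is shown, the stated power becomes less favourable.

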### Recruitment

Recruitment started in January 2019 and ended in December 2019. Although this study protocol was submitted for publication after the start of recruitment (due to usual writing, commenting, and approval procedures involving all coauthors), clinical trial registration took place prior to recruitment start. Participants were recruited in two orthopedic rehabilitation clinics located in southwestern Germany. In Germany, patients with severe injuries and chronic musculoskeletal conditions have the opportunity to receive rehabilitation therapies for 3 or more weeks in an orthopedic inpatient rehabilitation clinic covered by insurance companies. The target population in this study consists of persons with musculoskeletal conditions (e.g., arthritis, chronic back pain). Participants did not receive compensation for their participation. All consecutive patients are screened by a physician for eligibility upon arrival during their first medical examination. The first participant was enrolled on 7 January 2019, and the last patient was enrolled on 3 December 2019.

### Inclusion criteria

Patients are included if they fulfill the following inclusion criteria: (1) age 18 years or older; (2) musculoskeletal diagnosis classified in chapter M of the International Statistical Classification of Diseases and Related Health Problems, 10th Revision (ICD-10) [42], diagnosed by a physician; (3) sufficient knowledge of the German language; (4) ownership of a smartphone and internet access for online assessments; and (5) being physically inactive (sport activity < 30 min/week) in the last 3 months. Exclusion criteria are (1) rehabilitation following inpatient clinic treatment (e.g., due to surgery) and (2) not able to exercise for medical reasons. Eligible patients receive an invitation to participate in the study, an information letter/leaflet, and the informed consent form and complete the baseline online questionnaire (T0) during a study information meeting with a study assistant.

### Randomization

Randomization and allocation of participants to the two groups were done in advance by an independent researcher (CR) by means of a web-based program (https://www.sealedenvelope.com/) using permuted block randomization with variable block sizes of 2, 4, and 6 (randomly arranged) and a ratio of 1:1. Participants are stratified by center. The centers involved are two orthopedic clinics in southwestern Germany where recruitment is conducted consecutively. Participants are given randomly generated treatment allocations within sealed opaque envelopes. Once a participant is consented to participate in the study, the envelope is opened, and the patient is then offered the allocated treatment regimen. An independent researcher (CR) prepares the envelopes and is responsible for the allocation of participants to trial arms.

### Content of the face-to-face group intervention MoVo-LISA

The psychological group program MoVo-LISA (Motivation-Volition concept to support Lifestyle-Integrated Sports Activity; three to eight patients per group) is based on both motivation theories of health behavior [43–45] and volition theories of action planning and action control [46–48]. The theoretical framework underlying the MoVo-LISA intervention program is the MoVo process model. Its core idea is the differentiation between motivational and volitional strategies [21]. Motivational strategies are used to help form a strong and self-concordant goal intention. Volitional strategies are needed to implement competencies and action control [13]. MoVo-LISA is conceptualized as a short and economical psychological program based on a standardized curriculum. It has been developed specifically for an inpatient rehabilitation setting and has been shown to be effective in orthopedic patients [16, 17, 20]. In this trial, MoVo-LISA is offered to all randomized participants in both the intervention and control groups by the physiotherapists or sport and exercise therapists in each clinic. Before recruitment, all MoVo-LISA instructors were trained in the standardized program by the scientific project team during a 2-day course. In addition, a kickoff meeting was organized for all clinic staff in order to inform them about the study and to familiarize them with the MoVo concept.

The program MoVo-LISA consists of two group sessions and one individual session in which patients learn how to integrate physical activity into their daily lives. It does not consist of actual physical exercise but focuses on teaching the patients how to get and stay physically active after inpatient rehabilitation. The patients prepare specific activity plans for implementation in their everyday lives based on their individual needs and living context. Hence, the activity plans of the participants vary highly from aerobics to stretching and stabilizing exercises and are based on the recommendations that were developed during their orthopedic rehabilitation. In addition, they identify barriers that discourage them from being active and develop individual strategies to cope with those barriers. After discharge from the clinic, participants receive a postal reminder and a telephone interview. A detailed description is given by Fuchs and Göhner [16, 49]. The five main components of MoVo-LISA are listed in Table 1.

**Table 1 Tab1:** Elements of the MoVo-LISA program

Components	Time of event	Duration	Content/aim
First group meeting	Days 1–3 after clinic admission	60 min	To reflect on health goals and ideas for physical activity
Homework	After first group meeting	–	To prepare an individual activity plan
One-to-one interview	1 week after first group meeting	10 min	To refine the individual activity plan
Second group meeting	1–3 days before clinic discharge	90 min	To discuss barriers and barrier management to establish an activity protocol
Postal reminder	3 weeks after discharge		To remind patients of the two activity plans and the importance of their individual barrier management
Telephone call	5–6 weeks after discharge	10 min	To check the implementation of the activity plans and barrier management and to offer support in case of problems

### MoVo-App

The MoVo-App is based on the MoVo process model and was developed by a multidisciplinary team of psychologists, sport scientists, and computer scientists from the University of Freiburg. The aim was to develop an app that can be provided to individuals after clinic discharge subsequent to the group-based face-to-face intervention MoVo-LISA. The elements of the program are implemented within the MoVo-App to support participants in maintaining their acquired strategies and to put their activity plans into action within the upcoming 12 weeks after clinic discharge. We developed the MoVo-App for smartphones running iOS or Android operating systems.

After the installation of the MoVo-App, participants in the IG receive help with entering their health goals, activity plans, major barriers, and barrier management strategies developed during the MoVo-LISA group program into the app. Over the course of 12 weeks after discharge, the MoVo-App sends regular reminders to participants regarding their activity plan prior to the scheduled activity. Participants can record on the same day of the activity plan what percentage of their plan they have achieved in order to track their progress. Each week, participants are asked to evaluate their performance in terms of their satisfaction regarding the completion of their activity plans for that week. Participants can make adjustments to their activity plans or barrier management strategies if needed. All usage data of the app will be saved in the back end of the smartphone. At the end of the 12-week period, all users will be asked to finish the intervention and upload their usage data to a sharing platform (back4app.com) via a shortcut in the app. In addition to receiving the MoVo-App, participants in the IG have unrestricted access to TAU.

### Control condition

The control group receives MoVo-LISA during the clinic stay and has unrestricted access to TAU.

### Treatment as usual

TAU consists of a 3-week complex interdisciplinary and multimodal rehabilitation schedule. It comprises medical, physical, and psychological therapies specifically tailored to orthopedic patients. (More information on the German system of medical inpatient rehabilitation is given by Jäckel and colleagues [50]). Because TAU after clinic discharge may vary widely, TAU in this time will not follow a specific protocol.

### Assessments

The primary outcome is the level of sport activity that is assessed using the validated Movement and Sport Activity Questionnaire (BSA-F [51]). Secondary outcomes are movement activity, cognitive predictors of behavioral change, and health-related variables. According to the MoVo process model, it is necessary to change the underlying cognitions and self-regulatory skills in order to attain long-term behavior modification. The cognitive variables postulated by the MoVo process model assessed in this trial are sport-related self-efficacy, goal intention, self-concordance, action planning, perceived barriers, and barrier management, as well as sport-related consequence experiences. Experience of pain is considered a major health indicator among orthopedic patients. On the basis of the recommendations of the Initiative on Methods, Measurement, and Pain Assessment in Clinical Trials [52, 53], we selected pain-related outcome measures, including physical and emotional functioning. Demographic and clinical variables (e.g., age, sex, ICD-10 diagnosis), intervention adherence, and satisfaction are also assessed. The outcome measures and time points of interest are summarized in Fig. 1.

### Primary outcome

The level of sport activity in minutes per week is measured with the BSA-F [51]. This is a validated German self-report instrument used to measure the level of movement activities (functional physical activities of daily living; *see* “Secondary outcomes” section below) and sport activities (sport- and health-related exercises, such as soccer, jogging, Nordic walking, Pilates, or fitness training) in minutes per week. For the sport activity subscale, the participants list a maximum of three sport activities in which they have engaged within the last 4 weeks. For each activity episode, participants indicate the frequency and duration in minutes. Activities that do not target larger groups of skeletal muscles and do not lead to maintenance of or increases in endurance, power, coordination, or flexibility are classified as invalid activities for this group. For each valid activity, an activity amount in minutes per week is calculated by multiplying frequency and duration divided by 4. All single amounts of the named sport activities are added to obtain the individual’s score on the Sport Activity Index. The validity of the BSA-F has been shown in several studies. However, data do not permit an analysis of the reliability of the instrument [51].

### Secondary outcomes

#### Movement activity

Movement activity is measured with the BSA-F using the respective subscale [51]. The movement activity subscale consists of work- and leisure time–related movement activities within the last 4 weeks. Participants first rate their activity levels during work with regard to the frequency of (1) sitting (inversely coded), (2) moderate movement, and (3) intensive movement on a scale from 0 = not at all to 3 = a lot. Participants are then asked to indicate the duration in minutes per day and the frequency during the last 4 weeks for the eight most common movement activities in everyday life (e.g., riding a bike to work or carrying home groceries by foot). For each activity, an amount in minutes per week is calculated by multiplying frequency and duration divided by 4. These are added to obtain the individual’s score on the Movement Activity Index for the work- and leisure time–related movement activities separately.

#### Self-efficacy

In accordance with Schwarzer and colleagues [54–56], three different types of self-efficacy will be assessed: the belief that someone is able to (1) begin regular physical exercise, (2) maintain regular activity over a longer time period, and (3) resume regular activity after interruption. Each type of self-efficacy is measured with one item; the scores of the three items will be combined into one mean value. The response format is a 6-point Likert scale ranging from 0 = I don’t feel capable at all to 5 = I feel 100 per cent capable. An earlier study [15] yielded a satisfactory internal consistency ranging from α = 0.75 to α = 0.92 at different time points.

